# The YoungFitT project: Study protocol for a randomized mixed-methods trial of physical exercise and mind-body interventions, with or without virtual reality, in university students

**DOI:** 10.1371/journal.pone.0328538

**Published:** 2025-08-01

## Abstract

**Background:**

Mental health issues among young university students have increased in recent years, driven by academic stress and sedentary lifestyles. The YoungFitT Project aims to explore well-being strategies and the psychobiological mechanisms behind their effects on university students. The project includes two studies: the first evaluates the effectiveness of High-Intensity Functional Training (HIFT), Mindfulness-Based Stress Reduction (MBSR), and Qigong (QG) on psychological well-being and cognitive functions, and also explores whether socio-demographic, mental (mindful thinking, sleep quality), physical (physical fitness, physical activity), physiological (heart rate variability), and biological (microbiota) factors mediate or moderate intervention effects on university students. Given that immersive virtual reality (VR) can enhance adherence and provide additional benefits, the second study will explore the feasibility and efficacy of HIFT-VR, MBSR-VR, and QG-VR on university students’ psychological well-being and cognitive functions.

**Methods:**

Two mixed-methods randomized controlled trials will be conducted. In Study 1, participants will be randomly assigned to one of three groups (HIFT, MBSR, QG) using a 1:1:1 ratio. Psychological, cognitive, physical, physiological, and biological measures will be evaluated two weeks before and after the interventions. The interventions include three weekly sessions for 12 weeks. Subsequently, a follow-up will be conducted 12 weeks after the intervention to assess psychological well-being. Study 2 is a proof-of-concept study in which VR interventions will be co-designed with input from university students and professionals. Twelve participants from each study will also complete semi-structured interviews to explore their experiences and perceived impact.

**Discussion:**

The proposed interventions are expected to produce differential effects on psychological well-being and cognitive function. VR environments may enhance adherence and offer added benefits over conventional training. Findings will inform effective, personalized strategies for the mental and physical health of university youth.

**Trial registration:**

www.ClinicalTrials.gov, identifier NCT06406283; Registration date: 2024/05/06.

## Introduction

Mental health difficulties among youth represent a significant public health concern [1]. A particular focus is on emerging adults aged 18–25, a period that aligns with the onset of many mental disorders; indeed, 75% of such disorders begin before the age of 24 [2]. Notably, approximately 60% of young individuals within this age group are reported to be transitioning into university life, where they face numerous challenges, including academic pressures [3]. During this socially complex and stressful period, university students often engage in unhealthy behaviors, such as insufficient physical activity, potentially leading to a sedentary lifestyle that poses risks to both their mental and physical health [4]. Around one-third of the surveyed first-year university students were identified as likely experiencing at least one mental health disorder, such as anxiety or depression [5]. These mental health challenges can negatively affect various aspects of students’ lives, including emotional well-being, cognitive function, and academic performance. Enhancing cognitive abilities, such as memory and attention, is important not only for learning but also for coping with stress and maintaining psychological balance [6]. Therefore, there is an urgent need to develop and implement mental and physical health-boosting strategies that can be easily incorporated into a student’s daily routine. These strategies could be an effective way for students to manage stress, reduce anxiety, and enhance cognitive awareness, which in turn can lead to better health, productivity, and quality of life [7].

The benefits of physical exercise and mind-body interventions for psychological well-being have been highlighted. Physical exercise has been shown to have positive effects on psychological well-being and cognitive functions, particularly in older adults and children [8,9]. Emerging evidence also suggests similar benefits for young adults and university students [10,11]. As an exercise modality, High-Intensity Functional Training (HIFT) incorporates a mix of intense and varied movements to enhance overall physical condition [12]. HIFT stands out for its intensity, engaging more muscles and requiring greater cardiovascular effort than traditional workouts, while each session takes relatively little time. Its efficient, high-energy demanding format may appeal to busy young adults [12,13]. Growing research findings demonstrate HIFT can improve fitness-related measured in university students. A study comparing CrossFit, a training method similar to HIFT, with traditional weight training in university students found that both improved muscular strength and endurance and helped maintain body composition [14]. Moreover, when comparing High-Intensity Interval Running (HIIT-R) and HIFT in female university students, it was found that HIFT was as effective as HIIT-R in enhancing body composition and aerobic fitness. HIFT led to improved motor performance (sit-ups and standing broad jump), while the HIIT-R protocol showed no improvements [15]. Research on the cognitive and emotional effects of HIFT in university students is still limited. A study on a 10-week online HIFT program during the COVID-19 quarantine found improved reaction times without changes in psychological well-being. Nevertheless, the quarantine adversely affected adherence to the training regimen [16]. To our knowledge, this is the only study that has examined such a program in university students.

Mindfulness-Based Stress Reduction (MBSR) combines various mental and physical practices, such as mindful breathing, body awareness, and yoga, in group settings to promote well-being [17]. MBSR has become a popular tool for addressing the university mental health crisis and is now familiar to many young adults [18]. Substantial evidence supports the effectiveness of mindfulness-based interventions (MBIs) in improving mental health and well-being among university students. Numerous systematic reviews and meta-analyses have demonstrated small to moderate improvements in psychological well-being, particularly in alleviating anxiety, depression, and stress. While these findings are robust, the benefits for other aspects, such as sleep quality, life satisfaction, resilience, mindfulness, subjective well-being, and physical health, are more varied [19–26]. These inconsistencies might stem from differences in study designs, populations, or control conditions. In addition, evidence for cognitive improvements from MBIs in university students is limited, primarily due to the scarcity of studies within this population. A cross-sectional online study suggested that higher levels of mindfulness are associated with better cognitive functions but not with academic achievement [27]. In the context of mindfulness programs, one study reported increased speed in a cognitive flexibility task but no benefits in attention regulation [26]. Another study found no improvement in critical thinking performance following an online mindfulness intervention [28].

In recent years, Traditional Chinese Medicine has gained popularity across Western countries [29]. QG, one of its main branches, utilizes moving meditation practices that emphasize breathing to enhance mental and physical health [30]. QG emphasizes “Qi” (vital energy) and form to harmonize mind and body, promoting physical vitality and mental tranquility [31]. A meta-analysis focusing specifically on university students suggested that QG has the potential to enhance their physical (cardiorespiratory endurance and flexibility) and mental well-being (depression and anxiety). However, no statistically significant effects were observed for muscle strength, vital capacity, heart rate, or mood [32]. Moreover, another meta-analysis on university students with mild to moderate psychological symptoms showed that Traditional Chinese fitness exercises effectively improved depression, anxiety, and sleep disorders [33]. Regarding cognition, although Baduanjin form, one of the most widely practiced types of Health QG, has shown positive effects on executive functions in various populations, with potential benefits for memory, attention, and mental flexibility, there is limited research specifically focusing on university students [34].

Recent meta-analyses comparing different physical exercise and mind-body approaches have reported their specific effectiveness in improving mental health outcomes among young university populations. Subgroup analyses within these reviews reveal mixed results depending on the type of intervention and the specific mental health issue addressed [10,35–39]. For instance, some studies have reported that exercise-based interventions produce the largest effect sizes in improving depression and anxiety among university students [10,36,39], with one indicating that HIIT outperforms other strategies, including QG and Tai Chi [39]. Another study suggests that aerobic exercise may be more effective in reducing anxiety and stress, while traditional Chinese exercises might be particularly beneficial for managing stress [37]. These reviews highlight the need for direct comparisons between different physical exercise and mind-body interventions to better understand their relative effectiveness in addressing mental health outcomes. Notably, no study has directly compared the effectiveness of physical exercise, traditional Chinese practices, and mindfulness-based strategies. Furthermore, a significant gap exists in research comparing the effects of these interventions on cognitive functions in university students.

To better understand the effectiveness of physical exercise and mind-body interventions, exploring their psychobiological mechanisms is crucial. A recent systematic review identified twelve key mediators, including self-efficacy, self-esteem, resilience, and body image satisfaction, which strongly contribute to the positive effects of physical activity on mental health [40]. Among studies focused on university students, one demonstrated that the enduring effects of MBIs on stress are mediated by mindfulness and self-compassion [41]. In addition, another study highlighted the mediating role of self-regulation mechanisms such as attentional control, interoceptive awareness, and emotion regulation in improving young adults’ mental and physical health [42]. Furthermore, a pilot study found that QG’s effects on emotional regulation helped reduce symptoms of depression and anxiety in university students [43]. On the other hand, emerging research has also explored microbiota mechanisms underlying the effectiveness of physical exercise and mind-body interventions in healthy adults, with evidence suggesting a positive relationship between physical activity, cardiorespiratory fitness, and fecal short-chain fatty acid levels [44]. Mindfulness-based cognitive therapy has been shown to enhance bacterial diversity in individuals with high-trait anxiety [45], while practices like Tai Chi and Fitness QG have also been associated with improved intestinal flora health [46]. Despite these findings, the psychobiological mechanisms that explain the emotional and cognitive benefits of physical exercise and mind-body interventions, particularly the relationship between psychological and biological mediators, are poorly understood in young adults.

Translating benefits observed from lifestyle interventions into everyday practices can be challenging [47]. This is particularly evident among university students, who often struggle with maintaining consistent participation and adherence to well-being interventions [48,49]. In this context, technology-based interventions, such as virtual reality (VR) training, may offer an innovative strategy to boost adherence. Immersive VR places users in controlled, artificial environments where key features such as immersion, interaction, and presence can enhance enjoyment, motivation, and engagement, potentially improving treatment adherence [50]. Specifically, improved treatment adherence with MBI-VR has been observed in university students [41]. It has been suggested that VR can also improve long-term exercise adherence [51]. Regarding its effectiveness, VR-based exercise, focusing on traditional aerobic protocols, has shown positive outcomes in improving overall mood states [52] and enhancing working memory function [53] in university students. A systematic review examining VR-based well-being interventions (e.g., MBIs, relaxation, and meditation) in young adults indicated that VR could be an effective method for reducing stress and improving well-being in this population [54]. When compared to conventional mindfulness techniques, VR-based mindfulness training has been found to be more effective in adults [55]. Current research on the effects of VR with different physical exercise and mind-body interventions on psychological well-being and cognition in university students is still limited. Few studies have explored adherence, and none have directly compared their effectiveness. Challenges in this area include the poor use of randomized controlled trial (RCT) designs, variability in VR procedures, and the lack of comprehensive physiological measurements.

In addition to quantitative studies, qualitative research provides deep insights into personal experiences, perceptions, and behaviors. Findings from qualitative and mixed-methods studies have shown that mindfulness interventions improve mental health by reducing anxiety and stress, and by enhancing interpersonal relationships among university students. However, maintaining engagement and long-term practice remains challenging, especially in technology-based interventions [56–59]. Furthermore, QG has shown immediate and long-term benefits, including improved self-awareness, emotional resilience, and a stronger sense of community among students [60]. Several other qualitative studies have also examined mindfulness programs for healthcare students, demonstrating their effectiveness in reducing stress, improving emotional regulation, and enhancing focus. Despite time constraints, many students continued practicing mindfulness informally in their daily lives [61–63]. Qualitative VR studies have also explored mind-body interventions. In a multi-methods design, VR-based meditation enhanced engagement, mindfulness, and focus, with students reporting reduced stress. However, differences in anxiety and depression scores were not statistically significant, likely due to the small sample size [64]. Another study found interactive VR-based mindfulness training effective in improving mindfulness, engagement, and adherence, with the immersive experience boosting motivation and focus. This makes VR a valuable supplement to traditional mindfulness training in high-stress settings [65].

In conclusion, HIFT, MBSR, and QG represent promising well-being strategies. HIFT is an efficient, whole-body physical conditioning modality; MBSR offers a structured and widely accepted method for stress reduction; and QG offers an integrative practice that enhances mind-body harmony. These interventions have demonstrated benefits for psychological well-being and cognitive function in university students. However, to maximize their effectiveness and utilization, it is crucial to investigate the differences and overlap in their effects on various mental health outcomes, as well as to understand their mechanisms of action and the role of individual-level moderators. This can help identify which modality or combination of modalities is most effective in promoting mental well-being during emerging adulthood and may also reveal unique advantages specific to each approach. Furthermore, given their accessibility, cost-effectiveness, and suitability for busy students, these interventions show strong potential to enhance university student well-being, further justifying their study in this context. On the other hand, VR could effectively address issues of low engagement and persistence in training. Given university students’ familiarity with blended learning, they are well-suited for digital mental health support models.

### Objectives and hypotheses

The YoungFitT project, a mixed-methods RCT study, aims to investigate the effects and psychobiological mechanisms of online instructor-led physical exercise and mind-body interventions, as well as their VR-based counterparts, on psychological well-being and cognitive functions. The SPIRIT schedule of enrolment, interventions, and assessments is presented in Fig 1.

**Fig 1 pone.0328538.g001:**
[figure not shown]
Schedule of enrolment, interventions, and assessments. HIFT: High-Intensity Functional Training, MBSR: Mindfulness-Based Stress Reduction, QG: Qigong, VR: Virtual Reality.

The project includes two distinct studies:

**Study 1 delves into online physical exercise and mind-body interventions.** Its primary objective is to evaluate the effectiveness of HIFT, MBSR, and QG on the psychological well-being and cognitive functions of university students and to uncover potential mediators and moderators. Specifically, Study 1 aims to explore: (1) the effectiveness of HIFT, MBSR, and QG interventions on the psychological well-being and cognitive functions of university students; (2) the intervention-induced changes in physical aspects (physical activity and fitness status), mental aspects (mindful thinking and sleep quality), and physiological stress markers (heart rate variability [HRV]), and their potential mediating effects on psychological well-being and cognitive outcomes; (3) the intervention-induced changes in the microbiota and its potential mediating effect on psychological well-being and cognitive outcomes; and (4) the potential moderating effects of demographic factors (sex and age) and individual factors (cognitive reserve and general intelligence) on intervention-induced changes in psychological well-being and cognitive outcomes (see Fig 2).

**Fig 2 pone.0328538.g002:**
[figure not shown]
Key variables of interest in the YoungFitT study. HIFT: High-Intensity Functional Training, MBSR: Mindfulness-Based Stress Reduction Therapy, QG: Qigong, VR: Virtual Reality, HRV: Heart Rate Variability.

The key hypotheses for this objective are: (1) All three interventions will positively affect psychological well-being and cognitive functions at 12 weeks compared to baseline, with each intervention showing a specific profile of outcomes (HIFT: more cognitive gains; MBSR: more psychological gains; QG: moderate benefits in both areas). These positive effects are expected to persist at the 12-week follow-up; (2) All interventions are expected to induce changes in physical components (increased physical activity and fitness status), mental components (enhanced mindful thinking and sleep quality), physiological stress markers (increased HRV), and microbial composition (increased diversity), which will mediate improvements in psychological well-being and cognitive outcomes; (3) Sociodemographic factors (sex and age) and individual factors (cognitive reserve and general intelligence) will moderate changes in outcomes from pre- to post-intervention.

**Study 2 focuses on VR-based physical exercise and mind-body interventions.** The primary objective of this proof-of-concept study is to test the feasibility and preliminary effectiveness of VR-based HIFT, MBSR, and QG interventions on the psychological well-being and cognitive functions of university students. The specific objectives of this study include: (1) Generating virtual environments for HIFT, MBSR, and QG interventions; (2) Evaluating the usability, acceptability, and feasibility of these VR interventions; (3) Studying the effectiveness of VR interventions as depicted in Fig 2; and (4) Exploring the effects and adherence of these VR-based physical exercise and mind-body interventions compared to non-VR interventions.

It is hypothesized that: (1) All VR interventions will positively affect psychological well-being and cognitive functions after 12 weeks, with each intervention displaying distinct outcomes (HIFT: cognitive gains; MBSR: psychological gains; QG: moderate benefits); and (2) VR-based interventions will yield better adherence and greater benefits compared to non-VR interventions.

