## Materials and methods

### Study design

The YoungFitT project is a prospective, three-arm, parallel, single-blinded RCT mixed-methods study planned to be conducted in two phases, as illustrated in Fig 3. Study 1 will begin first, followed shortly by Study 2. Both studies adhere to the SPIRIT guidelines [66] (See S1 File). The Faculty of Psychology at the University of Barcelona will lead this interdisciplinary project, integrating expertise in neuropsychology, sports science, and computer science. The study protocol has been registered at ClinicalTrials.gov (identifier: NCT06406283) and approved by the institution’s Bioethics Committee (IRB number: IRB00003099; protocol code: CER112327) on October 18, 2023 (See S2 and S3 Files). It also complies with the ethical standards outlined in the Declaration of Helsinki. Eligible participants who agree to take part in the study will provide written informed consent. A member of the research team will obtain the signed consent form prior to conducting any baseline assessments. Protocol amendments will be updated on ClinicalTrials.gov and shared with regulatory bodies if necessary.

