### Statistical analyses

Data will be entered into a version-controlled Excel database. Analyses will be conducted using the latest available versions of IBM SPSS Statistics and R. A two-tailed p-value < 0.05 will denote statistical significance, with adjustments for multiple comparisons applied where appropriate. Descriptive statistics (means, standard deviations, medians, ranges, and frequencies) will summarize baseline characteristics overall and by group. We will assess distributional assumptions, including skewness and the presence of outliers. Missing data will be characterized by reporting the percentage of missing values for each variable and by evaluating the most likely mechanisms, classified as missing completely at random (MCAR), missing at random (MAR), or missing not at random (MNAR).

Primary hypotheses will be tested under an intention-to-treat (ITT) framework, including all randomized participants. Analysis of covariance (ANCOVA) will model change scores (post-intervention – baseline) using group, baseline score, and selected covariates as predictors. Sex and age will be included as covariates in all analyses. Additional covariates will be considered from a pool of theoretically relevant candidates if they show a significant and meaningful association with the outcomes. To minimize multicollinearity, we will examine the interrelationships among selected predictors and retain only one variable when substantial overlap is observed. If the omnibus test is significant, we will perform pairwise comparisons within each outcome variable using appropriate corrections for multiple comparisons (e.g., Bonferroni). Assumptions of homogeneity of regression slopes, normality, and homoscedasticity of residuals will be checked. If violated, alternative models (e.g., mixed-effects models for repeated measures) will be considered. Between-group findings will be supplemented by within-group analyses (paired t-tests or Wilcoxon tests, as appropriate).

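### With three active arms and no untreated comparator, the from-baseline clause of Hypothesis 1 rests on within-arm tests that cannot separate intervention effects from practice or calendar change

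*Protocol article*

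**What the plan says.** The abstract's Methods states that in Study 1 "participants will be randomly assigned to one of three groups (HIFT, MBSR, QG) using a 1:1:1 ratio", and Study design describes a "prospective, three-arm, parallel, single-blinded RCT mixed-methods study". No untreated, wait-list or attention-control arm is described.

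Under Objectives and hypotheses, the Study 1 aim is worded as efficacy: "Its primary objective is to evaluate the effectiveness of HIFT, MBSR, and QG". The first specific aim is "the effectiveness of HIFT, MBSR, and QG interventions on the psychological well-being and cognitive functions of university students", and later aims describe the pre-post changes in mediators as induced by the interventions. Hypothesis 1 begins "All three interventions will positively affect psychological well-being and cognitive functions at 12 weeks compared to baseline". The same sentence then predicts a different outcome profile for each arm, and the next sentence expects the gains to last to follow-up. Hypothesis 2 expects every intervention to change the mediators, and those changes to mediate the improvement.

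Statistical analyses assigns the primary hypotheses to an intention-to-treat model: "Analysis of covariance (ANCOVA) will model change scores (post-intervention – baseline) using group, baseline score, and selected covariates as predictors". It then adds: "Between-group findings will be supplemented by within-group analyses (paired t-tests or Wilcoxon tests, as appropriate". The significance rule is "A two-tailed p-value < 0.05 will denote statistical significance, with adjustments for multiple comparisons applied where appropriate".

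**The concern.** The opening clause of Hypothesis 1 is a causal statement about each arm on its own, with the arm's own baseline as comparator. Randomisation among three active arms supports statements about differences between arms. It does not say what would have happened to the same students with no programme.

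Two sources of change other than the intervention are plausible here:

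- **Practice.** The cognitive composites are primary outcomes. The tests are given before and after a 12-week programme and scored against the baseline distribution (Cognitive functions), so a retest gain passes straight into the change score. The article describes no alternate forms and no practice correction.
- **Calendar.** Recruitment is scheduled away from busy periods of the academic year (Recruitment), but nothing equivalent is stated for the post-test or follow-up. Randomising within each wave balances calendar effects between arms. It does not remove them from the change within an arm.

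If all arms improved alike, the ANCOVA would show no difference and any claim that the interventions work would rest on the paired tests alone. At stake is the answer to the study's stated primary objective.

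**Working it through.** **1. What the sample size covers.** Inputs from Sample size: three groups, f = 0.25, α = 0.05, power 0.80. With noncentrality λ = f²N, N = 159 gives λ = 0.0625 × 159 = 9.94, critical F = 3.054 and power 0.805. N = 156 gives 0.797, so 159 is the smallest total with equal groups. Allowing for 10% dropout, 159 / 0.90 = 176.7, or 177 (59 per arm). The plan's figures reproduce. They power the between-arm omnibus test, not improvement within each arm.

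**2. Where a common shift goes.** Write change = α + arm effect + γ × baseline + other covariates + error. A gain d shared by all arms turns α into α + d and leaves the arm effects unchanged. The ANCOVA is therefore unbiased for arm differences and silent on d. A within-arm paired test has d in its numerator.

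**3. Size of the effect on the paired test.** Assumptions, none given in the documents: no true intervention effect; a common gain of d baseline SDs; pre-post correlation r; equal SDs before and after. Evaluable n per arm = 159 / 3 = 53. The test is two-sided at 0.05 without multiplicity adjustment, and only significance in the direction of improvement is counted (nominal 2.5%).

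- Standardised mean change: dz = d / √(2(1 − r))
- Noncentrality: dz × √53
- Probability: P(noncentral t on 52 df > t at 0.975)

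Example, d = 0.3 and r = 0.7: dz = 0.3 / √0.6 = 0.387; noncentrality = 0.387 × 7.28 = 2.82; probability 0.790.

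| r | d = 0.1 | d = 0.2 | d = 0.3 | d = 0.4 |
|---|---|---|---|---|
| 0.5 | 10.7% | 29.8% | 57.3% | 81.5% |
| 0.7 | 15.0% | 45.4% | 79.0% | 95.8% |
| 0.8 | 20.3% | 61.8% | 92.3% | 99.5% |

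With 59 per arm the rates are slightly higher (for r = 0.7: 16.2%, 49.6%, 83.3%, 97.4%).

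**4. Trial-level view.** Simulation of three arms, 53 each, r = 0.7, 4,000 runs, no true effect:

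| Common gain d | ANCOVA omnibus significant | At least one arm improves | All three improve |
|---|---|---|---|
| 0 | 5.1% | 7% | 0% |
| 0.2 | 5.2% | 83% | 9% |
| 0.3 | 5.0% | 99% | 51% |

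The distortion is confined to the within-arm tests.

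**5. Mediation.** With arm as predictor, the indirect effect is a × b, where a is the between-arm difference in the mediator. If a mediator changes equally in all arms, a = 0 and a × b = 0 however large the shared change. Hypothesis 2 can therefore be tested only as between-arm differences.

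**The case against.** The strongest reply is that this is a comparative trial and is analysed as one. The introduction argues for direct comparisons, the sample size is for a three-group omnibus test, the primary hypotheses are assigned to the randomised ANCOVA, and the within-group tests are labelled supplementary. The profile half of Hypothesis 1 is tested properly. All of this stands, and it limits the point to the from-baseline clause, the effectiveness wording and the reading of the paired tests. It does not rescue the clause, because those supplementary tests are the only ones that address it.

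A reader might infer several stronger things that the documents do not support:

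- **That the trial will very likely report cognitive benefit even if nothing works.** This depends on an assumed practice gain and correlation. At 0.1 SD the per-arm rate is 11% to 20%. The hypothesis concerns all three arms, and at 0.2 SD with r = 0.7 all three are significant in only 9% of simulated trials.
- **That regression to the mean inflates the changes.** Eligibility sets no threshold on symptoms or cognition, so the design does not select extreme baseline scores.
- **That calendar change must favour the interventions.** Recruitment timing is a partial mitigation, and a post-test near examinations could mask a real benefit.
- **That mediation shares the flaw.** Equal mediator changes cost sensitivity; they do not create a false claim. The Discussion also expects the changes to vary by intervention.

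**Conclusion.** The concern holds for one clause of Hypothesis 1 and for the wording that treats pre-post change as effectiveness or as caused by the intervention. The design can show which intervention does better, and for which outcomes. It cannot show that any of them works against no intervention. No later analysis detail can supply the missing concurrent comparator.

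Under the assumptions stated (gain 0.1 to 0.4 SD, r 0.5 to 0.8, 53 per arm, no true effect), a given arm's paired test shows improvement in about 11% to 99.5% of trials instead of 2.5%. Multiplicity adjustment would lower these rates but would not remove the shift that causes them. If no common shift exists, there is no inflation. The randomised ANCOVA, the sample size and the between-arm conclusions are unaffected. Hypothesis 2 needs the same restatement, because shared changes give no between-arm indirect effect.

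**What to change.** 1. Restate the first objective and Hypotheses 1 and 2 as differences between HIFT, MBSR and QG, keeping the predicted profiles.
2. In place of the paired t and Wilcoxon tests, report arm-level mean changes with 95% confidence intervals from the primary model, labelled descriptive.
3. State that change from baseline includes practice and calendar effects and is not evidence of effectiveness against no intervention. This sentence does the work: an interval that excludes zero is confounded in the same way as a paired test, so dropping p-values alone would not help.

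The cost is a short amendment to the protocol and registry entry, for which Study design already provides a route. The analysis of the randomised comparison does not change. The downside is that the trial gives up a claim its design cannot support. Keeping that claim would need a concurrent control arm. Recruitment began in February 2024, so an arm added now would not be concurrent with the earlier waves.
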